#### Exclusion criteria

Patients will be excluded from the cohort(s) if they: have less than 1 year of active data in their participating practice before the index date; and/or who have a Read code for coronary heart disease, congestive heart failure or cardiomyopathy, and/or stroke before the index date. A flow diagram will present the selection and exclusion (with reasons where possible) of patients in the study.

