#### Duration of follow-up

Patients will be followed up in the database from their index date until the earliest of the following: date of death; date of outcome of interest; date of leaving the participating practice; date of the latest download of data; or the end of the study follow-up period (ie, up to 22 years).

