### Outcomes

The primary aim of objective 1 is to assess the impact of an SMI diagnosis on weight change. A pilot search of the database indicated waist circumference was not reliably recorded so we did not include this as a measure of adiposity. The outcome for objective 2 is change in cardio-metabolic risk factors for CVD, which include change in systolic and diastolic blood pressure, change in total cholesterol/high-density lipoprotein ratio, and change in glycaemia indicated by HbA1c or fasting glucose. The outcome for objective 3 is incidence of and mortality from CVD. The objective for 4 is coded weight management advice and referral to weight management services. We will interpret the data based on the associations for all outcomes, as well as consistency and interpretable patterns. The specific outcomes for each objective are outlined in table 1.

**Table 1 T1:** Outcome measures

Objective	Outcome	Measures
Objective 1: Examine the association between SMI and weight change	Weight change	Absolute mean weight change (kg)
		Percentage weight change (kg)
		Change in body mass index (kg/m^2^)
Objective 2: Examine the association between SMI and changes cardio-metabolic risk factors for CVD	Cardio-metabolic risk	Change in fasting blood glucose (FBG)
		Change in haemoglobin A1c (HbA1c)
		Change in mean total-cholesterol
		Change in triglycerides
		Change in low-density lipoprotein (LDL)
		Change in blood pressure (systolic (SBP) and diastolic (DBP))
Objective 3: Total incident and fatal CVD	Incidence of CVD and CVD fatalities	Angina diagnosed by GP
		Acute coronary syndrome
		Coronary heart disease
		Congestive heart failure
		Cardiomyopathy
		Total stroke
		Total fatal CVD events
Objective 4: Weight management advice and service referral	Proportion (%) of exposed and unexposed who are recorded as offered advice, and then offered and actually referred to a weight management service	

CVD, cardiovascular disease; GP, general practitioner; SMI, serious mental illness.

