### Variable library

Exposures, outcomes and covariates of interest will be identified using medical coding (Read/SNOMED/EMIS), product coding (DM+D) and recording of patient death or transfer out of a participating practice in CPRD Aurum. The final definitions and code library has been drawn up and validated through consensus agreement among all investigators.

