### Statistical analysis

Analyses will be conducted in Stata using an estimation approach. We do not intend to impute missing data. The entry date into the analysis is the index date. The outcome date is the earliest of: (1) the date of death or (2) date of diagnosis of the outcome of interest. For objectives 1 and 2, we will use all repeated measures and run separate models for each analyses. For objective 3, we will use the first recorded diagnosis of the outcome of interest rather than recurrent events. Patients who do not have the outcome of interest will be censored at the earliest of: (1) date of death, (2) date of leaving the practice, (3) date of the latest download of data or (4) the study end date.

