#### Sensitivity and secondary analyses

If necessary, data on missing confounders and covariates will be addressed by adjusting for missingness as a category. Sensitivity analyses will examine the impact of running the analyses with everyone included as discussed above and confined only to those with complete data. A second sensitivity analysis will be performed excluding patients that experience the outcome within 2 years of the SMI Read code to avoid reversed causality from other underlying disease.

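### The pre-index exclusion does not name angina or acute coronary syndrome, which Table 1 counts as objective 3 outcomes; unless the coronary heart disease codes cover them, prevalent disease can be counted as incident CVD

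*Protocol article*

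**What the plan says.** Under Exclusion criteria, the protocol article removes patients "who have a Read code for coronary heart disease, congestive heart failure or cardiomyopathy, and/or stroke before the index date".

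Under Outcomes, it states: "The outcome for objective 3 is incidence of and mortality from CVD". Table 1 then gives objective 3 seven rows: six diagnoses and total fatal CVD. Two of the six diagnoses, "Angina diagnosed by GP" and "Acute coronary syndrome", have rows of their own, apart from the row for coronary heart disease.

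On timing, Duration of follow-up says: "Patients will be followed up in the database from their index date until the earliest of the following". For objective 3, Statistical analysis says: "we will use the first recorded diagnosis of the outcome of interest rather than recurrent events". Neither section says what happens to a patient whose first such diagnosis predates the index date.

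The codes behind each label are in a library that the article describes but does not show: "The final definitions and code library has been drawn up and validated through consensus agreement among all investigators".

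**The concern.** An incidence analysis needs an at-risk set free of the outcome at time zero. The exclusion list evidently aims at that, since every condition it names is also a Table 1 outcome. The list is shorter than the outcome list, however. Consider a patient with GP-coded angina before the index date and no code for an excluded condition. On the labels as printed, this patient is eligible, and the next angina, ACS or coronary heart disease code after index could be scored as new CVD.

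If that happens, some of the counted events are old disease being re-recorded. The comparison then mixes the effect of SMI on new CVD with the ratio of prior angina and ACS prevalence in the two groups. That ratio need not be 1, because GP contact and the recording of heart disease may differ between people with SMI and controls. A large cohort does not help: it narrows the interval around a biased estimate.

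**Working it through.** **1. The two lists side by side**

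| Diagnosis | Named in Exclusion criteria | Objective 3 row in Table 1 |
|---|---|---|
| Angina (GP diagnosis) | no | yes |
| Acute coronary syndrome | no | yes |
| Coronary heart disease | yes | yes |
| Congestive heart failure | yes | yes |
| Cardiomyopathy | yes | yes |
| Stroke | yes | yes |

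Four of the six diagnoses match by label and two do not. No other section excludes prior angina or ACS.

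**2. Does the first-diagnosis rule close the gap?** The rule limits each patient to one event. It does not define who is at risk. Suppose a pre-index angina code counts as the first diagnosis. The outcome date then precedes entry, and the Cox model cannot use it. There are three ways to proceed:
- drop the patient, which the article does not say;
- count the next code, which scores old disease as new;
- keep the patient as event-free, which adds person-time that cannot yield that outcome.

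If the rule is applied component by component, a patient with pre-index angina and a first ACS or coronary heart disease code after index is counted in any case.

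**3. The plan's own figures.** Sample size calculation gives 1% per year over 3.2 years, rounded to 3%, and a relative risk of 1.3. Take p1 = 0.039 (exposed), p2 = 0.030 (unexposed), k = 4 unexposed per exposed, 80% power and two-sided alpha 5%. The pooled risk is (0.039 + 4 × 0.030)/5 = 0.0318, and

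n = [1.960 × √(1.25 × 0.0318 × 0.9682) + 0.842 × √(0.039 × 0.961 + 0.030 × 0.970/4)]² / 0.009² = 3907 exposed.

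The printed 3907 is reproduced, and this point does not change it.

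**4. Illustrative size.** From the protocol: rate 1% per year, 3.2 years, relative risk 1.3. Assumed, because the documents give no values: prior angina/ACS prevalence p (pe in exposed, pc in unexposed) among entrants, and probability r that such a patient is re-coded during follow-up.

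Risk in disease-free unexposed: 1 − exp(−0.01 × 3.2) = 3.15%.

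Share of counted unexposed events that are prevalent disease = p·r / [p·r + 0.0315·(1 − p)]:
- p = 0.5%, r = 0.3: 0.0015/(0.0015 + 0.0313) = about 5%
- p = 2%, r = 0.6: 0.0120/(0.0120 + 0.0309) = 28%

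Observed RR = [1.3 × 0.0315·(1 − pe) + pe·r] / [0.0315·(1 − pc) + pc·r]. With r = 0.5:

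| pe | pc | Calculation | Observed RR |
|---|---|---|---|
| 1% | 1% | 0.0455/0.0362 | 1.26 |
| 0.5% | 1.5% | 0.0432/0.0385 | 1.12 |
| 1.5% | 0.5% | 0.0478/0.0338 | 1.41 |

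A second set of assumptions, using the rounded 3% baseline, gives a similar picture. With equal prevalence of 0.5% to 2% and re-coding of 30% to 90%, the observed RR runs from about 1.29 down to 1.19. With 60% re-coding, 2% exposed against 1% unexposed gives 1.41, and the reverse gives 1.08.

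**The case against.** The strongest objection is that coronary heart disease is commonly used as an umbrella term for angina and ACS. Separate rows in Table 1 do not prove separate definitions: the fatal-CVD row already cuts across the disease rows, and a table may list an umbrella beside its parts. The code library settles the matter and is not shown, and a condensed article can leave code-list scope to the full document. This stands. It is why the consequence is conditional, and on that reading the effect is nil. It does not remove the need for a sentence, because the term would then be an umbrella in the exclusion while its parts are listed separately among the outcomes, and the article does not say so.

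A second objection is that the first-diagnosis rule rejects recurrent events, and that at least a year of pre-index data is required, so earlier codes are visible. A post-index repeat would then not be a first record. The wording does lean that way, most clearly if the outcome of interest is total CVD as a composite. It still does not remove the patient from an analysis that starts at index, and it does not settle a change of code from angina to ACS.

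A third objection is the planned sensitivity analysis "excluding patients that experience the outcome within 2 years of the SMI Read code to avoid reversed causality". It would catch some early re-coding. But it leaves the primary analysis unchanged, misses re-coding after two years, and is anchored on a code that unexposed patients never have.

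Finally, the prevalence, re-coding and imbalance inputs are all assumed, and the larger shifts come only from the assumed imbalance. This is correct, and the figures are illustrations only.

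**Conclusion.** The mismatch between the two lists is a matter of text and is established. As written, pre-index angina and ACS are not named in the exclusion, although both are objective 3 outcomes. The bias is conditional. It arises only if the coronary heart disease exclusion codes omit angina and ACS, and if a later code in such patients is counted or the patients otherwise stay in the at-risk set.

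A reader might infer that patients with prior angina or ACS certainly enter and that their next code will be scored as a new CVD event. The documents do not support that, because the code lists are unseen and the handling of pre-index records is not stated. Nor do they support a claim about direction. On the assumptions above, a true relative risk of 1.3 falls to about 1.26 with equal 1% prevalence and 50% re-coding, and lies between 1.12 and 1.41 when prevalence differs threefold in either direction. The calculation also assumes that re-coding is equally likely in both groups, and it works with risk ratios rather than hazard ratios. Severity is moderate.

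**What to change.** In Exclusion criteria, make the pre-index exclusion for objective 3 identical to the Table 1 diagnosis list by adding angina and ACS. Identify them with the same code lists that define the outcomes, in exposed and unexposed patients alike. In Statistical analysis, add that a pre-index record of any component removes the patient from the incident-CVD analysis. If the coronary heart disease codes already include angina and ACS, say so; the change is then one of wording only.

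The cost is a sentence or two and reuse of existing code lists, plus a small loss of patients with prior angina or ACS. Against the 135 870 patients with SMI in the feasibility count and the 3907 required, that loss should not matter for power. The change is best made before the objective 3 analysis set is fixed.

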#### Duration of follow-up

Patients will be followed up in the database from their index date until the earliest of the following: date of death; date of outcome of interest; date of leaving the participating practice; date of the latest download of data; or the end of the study follow-up period (ie, up to 22 years).

#### Comparison group

The unexposed represents the counterfactual and will include patients without an SMI Read code ever (hereafter *unexposed*) drawn from the source population. Up to four unexposed matches will be selected at baseline only if they have a qualifying weight Read code within±one year of the index date to the exposed in which they are matched. The matching variables include: age, sex, practice and calendar time. All weight Read codes will be extracted.

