#### Study cohort

We will select a study cohort from the CPRD Aurum to investigate objectives 1–3. We will identify and extract the records in the primary care and HES dataset for all patients with a diagnosis of SMI (hereafter *exposed*) and who are eligible for data linkage. Diagnostic Read codes, which are the standard clinical codes used in UK general practice, will be used to identify an SMI diagnosis. We will also use codes according to the International Classification of Diseases version 10 (ICD-10) from the HES data. The date of the first SMI Read code will be used as the index date, which is the earliest date that an exposed patient may enter the study. From the study cohort, a subcohort of patients will be selected to investigate objective 4. To enter the subcohort, the exposed patient needs a recorded BMI ≥25 kg/m^2^ at any time after the index date. All information will be extracted for the period 01 January 1998 to 31 October 2020—the earliest and latest dates respectively that data are available.

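### Controls are selected at baseline but must never receive an SMI code, so their eligibility depends on the future; the bias differs by outcome and is probably small

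*Protocol article*

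**What the plan says.** All references are to the protocol article.

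- **Comparison group:** the unexposed "will include patients without an SMI Read code ever". The same paragraph sets the time of selection: "Up to four unexposed matches will be selected at baseline". It also describes this group as the counterfactual for the exposed.
- **Study cohort:** for the exposed, "The date of the first SMI Read code will be used as the index date". Nothing is required of their records after that date.
- **Exclusion criteria:** a patient is left out if there is a "Read code for coronary heart disease, congestive heart failure or cardiomyopathy, and/or stroke before the index date".
- **Duration of follow-up:** "Patients will be followed up in the database from their index date". Follow-up ends at death, the outcome, leaving the practice, the last data download or the end of the study period, which allows up to 22 years.
- **Statistical analysis:** "Patients who do not have the outcome of interest will be censored at the earliest of" death, leaving the practice, the last download or study end. A first SMI code in a control is in neither list.
- **Sensitivity and secondary analyses:** these cover missing covariates, complete data, and exclusion of outcomes within two years of the SMI code. None changes how controls are defined.

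**The concern.** The absence of any SMI code at any time cannot be known at baseline. A patient who is SMI-free on the matched index date but is first coded years later is rejected because of something that has not yet happened. The plan does not censor such a person at the code; it removes the whole record.

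The condition also reaches beyond the control's own follow-up. In the CVD analysis a control's follow-up stops at the CVD event, yet an SMI code recorded after that event still removes the control and the event. The same person cannot enter as exposed either, because one of the listed CVD conditions now precedes the SMI index date. The event occurred in SMI-free time and is lost from both groups.

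At stake is the comparison in objective 3. A group defined by hindsight does not exist at time zero, and so does not match the counterfactual role that the protocol gives it. Because the rule acts differently on fatal and non-fatal events, it could also produce a difference between the incidence and mortality results that readers could not tell from a real one.

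**Working it through.** **1. The plan's own figure.** Sample size calculation gives 3% CVD risk over 3.2 years, RR 1.3, ratio 0.25, 80% power and n = 3907. With p0 = 0.03, p1 = 1.3 × 0.03 = 0.039 and two-sided 5%, the two-proportion formula gives 15,628 unexposed and 0.25 × 15,628 = 3,907 exposed. The figure reproduces as the number of exposed. The way controls are defined does not enter it.

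**2. Inputs for the bias.**

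- CVD hazard λ = 0.01 per year and true HR = 1.30 (Sample size calculation, the RR taken as the HR).
- Follow-up τ = 3.2 years (the feasibility median for the exposed) and 22.8 years (the full window, 1 January 1998 to 31 October 2020).
- *Assumed, not in the document:* SMI hazard in controls σ = 0.05% per year, multiplied by θ = 1, 2 or 5 after non-fatal CVD.

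**3. Model with constant hazards.** A control is free of both CVD and SMI at time t with probability S(t) = exp(−(λ+σ)t). If controls are censored at a first SMI code, the CVD rate is λ∫S / ∫S = λ = 0.01. Under the never-SMI rule an event at time t is kept with probability k(t), where k(t) = exp(−θσ(τ−t)) for a non-fatal event and k(t) = 1 for a fatal one. The share at risk at t is then S(τ) + ∫ₜ^τ λS(u)k(u)du. Distortion of the HR = 0.01 ÷ (never-SMI control rate).

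**4. Fatal events by hand, τ = 22.8.**

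- S(τ) = exp(−0.0105 × 22.8) = 0.7871.
- Events per control = (0.01/0.0105) × (1 − 0.7871) = 0.2028 under either definition, since nobody is coded after death.
- Person-years with censoring = 0.2129/0.0105 = 20.276.
- Person-years under never-SMI = 22.8 × 0.7871 × (0.0005/0.0105) + 20.276 × (0.01/0.0105) = 0.855 + 19.311 = 20.165.
- Control rates are 0.01000 and 0.010055, so the distortion is 0.9945 and 1.30 becomes 1.293.

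**5. Results at σ = 0.05% per year.**

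| Outcome | θ | 3.2 years: distortion, HR | 22.8 years: distortion, HR |
|---|---|---|---|
| Non-fatal | 1 | 1.000, 1.300 | 1.000, 1.300 |
| Non-fatal | 2 | 1.0008, 1.301 | 1.0055, 1.307 |
| Non-fatal | 5 | 1.0032, 1.304 | 1.0221, 1.329 |
| Fatal | – | 0.9992, 1.299 | 0.9945, 1.293 |

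**6. Converters who differ in CVD risk.** If a share s of controls is removed and their CVD rate is k times that of the rest, observed HR = 1.30 × [(1−s) + sk]. A rough value is s = 135,870/16,000,000 = 0.85%. It is rough because the 16 million are current registrants and the SMI count is not said to be. The result is 1.289 at k = 0, 1.300 at k = 1, 1.322 at k = 3 and 1.344 at k = 5.

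**7. Extreme case.** Treating the whole 0.85% as new codes within 3.2 years gives σ = 0.0085/3.2 = 0.27% per year. Over 22.8 years the distortion is 0.97 for fatal events (HR 1.263) and 1.12 for non-fatal events with θ = 5 (HR 1.458).

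**The case against.** The strongest case on the other side concerns direction and size. Removing later converters takes away their person-time as well as their events. If SMI coding is unrelated to CVD, the two fall in proportion and nothing is distorted. For deaths the bias runs towards a weaker association. At the median follow-up of 3.2 years the distortion is at most 0.3% under the central assumption. All of this stands.

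A reader might infer that the rule inflates the SMI–CVD association in general. For example, if 0.3% of all controls and 1–5% of those with a CVD event are later coded, 1.30 × 0.997/(1 − q) gives 1.309 at q = 1% and 1.364 at q = 5%. The document does not support that reading. The range assumes that coding is about 3 to 17 times as frequent after CVD as among controls overall (1/0.3 to 5/0.3), and no section gives such a figure. At q = 0.3% the formula returns 1.30, and at q = 0, the fatal case, it returns 1.296. The planned exclusion of outcomes within two years of the SMI code shows that the investigators have underlying physical disease in mind, but it supplies no rate.

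The remedy also has costs. The Exposures section says diagnoses are clarified over time, and the Discussion says first prescriptions may be missed, so some illness before the first code would fall into control time. Censoring at the SMI code may be informative if coding is related to CVD. Both points are fair. They call for a sensitivity analysis and do not justify selecting controls on their future.

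**Conclusion.** The design flaw is established by the text: control eligibility depends on information after the index date, no censoring rule or sensitivity analysis repairs it, and some CVD events are counted in neither group.

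The direction depends on the outcome. For non-fatal CVD it is upward only if SMI coding is more frequent after CVD or converters carry a higher CVD risk; the document states neither. For fatal CVD and all-cause mortality it is downward, because only event-free person-time is removed.

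With an assumed SMI hazard of 0.05% per year, two- to five-fold higher after CVD, a true HR of 1.30 is reported as about 1.30–1.33 for non-fatal events and 1.29–1.30 for fatal ones. Larger shifts need the extreme inputs of the last step of the working. The bias is therefore probably small. It is systematic, however, so the large number of SMI patients will not average it out. For weight, cardio-metabolic change and referrals the same selection applies, but neither direction nor size can be derived from the document.

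**What to change.** In Comparison group, define the unexposed as patients with no SMI code on or before the matched index date. In Duration of follow-up and Statistical analysis, add a first later SMI code to the censoring events for controls. From that date the patient may enter as exposed if otherwise eligible. Keep the never-SMI definition as a sensitivity analysis; the difference between the two results then shows how much the choice matters for each outcome.

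The cost is a few sentences and one date that is already in the records. The sample size stays at 3,907 exposed. The downsides are a little more bookkeeping when one patient contributes to both groups at different times, some pre-diagnosis illness in control time, and possibly informative censoring.

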### Data linkage

Data will be linked to the Hospital Episode Statistics (HES) and the Office for National Statistics mortality databases. Data linkage to the practice level Index of Multiple Deprivation (IMD), as a proxy measure for socioeconomic status (SES), will also be used when describing the baseline characteristics in the descriptive analyses and in secondary analyses.

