### Confounding

We have identified confounding variables using directed acyclic graphs (DAGs), which aims to theoretically formalise potential confounders, colliders and biasing relationships.^26^ The DAG for each objective is described in online supplemental material S1. The DAG for objective 1 shows one direct path from the exposure (ie, SMI) to the outcome (ie, weight change), and four indirect paths: via health behaviours (ie, alcohol use, smoking and diet), SES status, psychotropic medication, and healthcare access and provision. Diet and physical activity are latent variables in CPRD Aurum because they are unmeasured. There are three confounding paths: via age, sex and ethnicity.^27 28^ Thus, the minimally sufficient adjustment for the total effect of SMI status on weight is to adjust for age, sex, and ethnicity.

10.1136/bmjopen-2021-053427.supp1Supplementary data

Frequency matching will ensure our ability to adjust for confounding variables that include age, sex, and calendar year, and matching on practice will remove practice-specific variables. In addition, we will fully adjust our models by considering several covariates in the relationship between the exposure and outcome (see table 2). All categorical variables will be analysed using the natural reference category as the reference group. Data on individual prescriptions for psychotropic and cardio-metabolic medications will be extracted from the primary care data from index date until censoring. For psychotropic medications, drugs will be classified according to the British National Formulary. For objectives 2 and 3, we will assess the impact of weight gain on change in cardio-metabolic risk factors and incidence of CVD using mediation analysis to allow us to estimate the direct (unmediated) and indirect (mediated) effects of SMI on CVD risk and incidence. To do this, we will fit two regression models: one regressing the outcome on the exposure, adjusting for confounders and another regressing the mediator on the exposure and confounders using the Stata *Med4way* command to estimate mediated effects.^29^ For objective 4, we will assess the presence of confounding by comparing estimates with and without adjustment. We will use Read codes, which have been previously developed by our team, to identify outcome and covariate records.

**Table 2 T2:** Confounders

Confounders and covariates		Measures

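### Hospital (HES) codes help define who has SMI, but the index date, the unexposed group and the prior-CVD exclusion rest on Read codes only

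*Protocol article*

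**What the plan says.** All references are to the protocol article.

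- **Exposed (Study cohort).** Two sources are used: "We will identify and extract the records in the primary care and HES dataset for all patients with a diagnosis of SMI". After naming Read codes as the general-practice coding system, the section adds: "We will also use codes according to the International Classification of Diseases version 10 (ICD-10) from the HES data".
- **Index date (Study cohort).** "The date of the first SMI Read code will be used as the index date".
- **Unexposed (Comparison group).** The group "will include patients without an SMI Read code ever (hereafter *unexposed*) drawn from the source population".
- **Prior CVD (Exclusion criteria).** Patients are excluded "who have a Read code for coronary heart disease, congestive heart failure or cardiomyopathy, and/or stroke before the index date".
- **Linkage (Data linkage; Source population).** "Data will be linked to the Hospital Episode Statistics (HES) and the Office for National Statistics mortality databases". The source population is limited to patients who are eligible for linkage.
- **Outcomes (Confounding; Statistical analysis).** "We will use Read codes, which have been previously developed by our team, to identify outcome and covariate records". For objective 3 the event is the first time the outcome appears in the record, and recurrences are not used.
- **Sensitivity analysis.** One secondary analysis drops patients whose outcome falls within 2 years of the SMI Read code.

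**The concern.** Two sources decide who is exposed, but one source decides when follow-up starts, who may serve as a control and who is free of CVD at entry. Three things follow.

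- **Group membership is not exclusive.** The rules place a patient with SMI coded only in HES in both groups and give that patient no start date. A programmer would have to make an undocumented choice.
- **Time zero can be late.** A patient diagnosed in hospital and GP-coded later enters at the later date. The Introduction links psychotropic drugs to rapid weight gain, and the Discussion accepts that first prescriptions issued in secondary care may be missed. Part of the early change that objective 1 is meant to capture may therefore precede entry.
- **Old CVD can be counted as new.** A hospital-only stroke or infarction before entry passes the exclusion. If it is later entered in the GP record, it becomes the first recorded event for objective 3.

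The feasibility count is 135 870 patients with SMI, against a stated minimum of 3907. Random error will be small, so systematic error of this kind will matter more than precision.

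**Working it through.** **1. The rules side by side**

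| Rule | GP Read codes | HES ICD-10 codes |
|---|---|---|
| Exposed | yes | yes |
| Index date | yes | not named |
| Unexposed | yes | not named |
| Prior-CVD exclusion | yes | not named |
| CVD outcomes | yes | not named |

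Take a patient with a HES SMI code and no SMI Read code. Exposed: yes. Index date: none. Unexposed: also yes.

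**2. The plan's own figure.** Inputs from the Sample size calculation section: 3% CVD over 3.2 years in the unexposed, relative risk (RR) 1.3 (so 3.9% in the exposed), exposed-to-unexposed ratio 0.25, 80% power. The two-proportion formula at two-sided 5%, without continuity correction, gives 15 628 unexposed and 15 628 × 0.25 = 3907 exposed. The stated 3907 is reproduced. The present point does not depend on it, but 3% and 3.9% serve as the base below.

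**3. Contamination of the unexposed.** Let c be the share of the unexposed who have HES-only SMI (assumed). RR = 3.9 / [3(1 − c) + 3.9c].
- c = 0.1%: 1.2996
- c = 1%: 3.9 / 3.009 = 1.296
- c = 2%: 3.9 / 3.018 = 1.292

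This is negligible.

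**4. Prior CVD passing the exclusion, moderate assumptions.** Let q be the prevalence of prior CVD, m the share of it known only in HES, and r the share of those patients recorded with CVD during follow-up. All three are assumed. Counted risk = p(1 − qm) + qmr, with p = 0.03 or 0.039.
- q = 5% in both groups, m = 5%, r = 20%: exposed 0.0394, unexposed 0.0304, RR 1.295. Non-incident share of counted events: 1.3% exposed, 1.6% unexposed.
- q = 5% in both groups, m = 25%, r = 50%: exposed 0.0448, unexposed 0.0359, RR 1.248. Non-incident share: 14.0% exposed, 17.4% unexposed.
- q = 6.5% exposed and 5% unexposed, over the same ranges of m and r: RR 1.295 to 1.299, with up to about 17% of counted events in each group not incident.

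**5. Prior CVD passing the exclusion, every missed case re-coded during the 3.2 years.**
- 1% of each group: (3.9 + 1) / (3 + 1) = 4.9 / 4.0 = 1.23
- 2% of the exposed, 1% of the unexposed: (3.9 + 2) / (3 + 1) = 5.9 / 4.0 = 1.48

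The bias can go either way, depending on how missed prior CVD is spread between the groups.

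**6. Late entry.** The article gives no lag between hospital and GP coding, no share of patients diagnosed first in hospital and no weight-gain figure in kg. The direction is plausible, but no size can be derived.

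**The case against.** The strongest reply is that the article is condensed, that Read code may be shorthand for any diagnostic code, and that the code lists are not shown. This does not carry the SMI rules, because the Study cohort section itself separates Read codes from HES ICD-10 codes and then uses only the former for the index date.

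A second reply is that the 2-year sensitivity analysis removes early re-coded events. It does remove some, but it leaves the primary analysis as it is, also discards true early events, and changes neither the index date nor the unexposed definition. Its clock runs from the SMI Read code, and how it applies to the unexposed is not stated.

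Several stronger readings are tempting, but the article does not support them:

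- **Hospital-only CVD events will be missed.** The article says Read codes will be used for outcomes, not that nothing else will be. HES and mortality data are linked, and Table 1 marks only one outcome as GP-based ("Angina diagnosed by GP"), which hints at other sources for the rest. The outcome source is unclear; a loss of events is not shown.
- **Angina and acute coronary syndrome are left out of the exclusion.** Both are forms of coronary heart disease, which is excluded, and the rows of Table 1 overlap. The wording could be clearer, but an omission is not established.
- **First-year hazard ratios of (1.3 + 1)/(1 + 1) = 1.15 or (1.3 + 2)/(1 + 1) = 1.65 show the impact.** These require every missed case to be re-coded in year 1, and they describe one year rather than the study.
- **Weight gain is understated by a definite amount.** Any kg figure would be wholly assumed. The feasibility cohort has a weight record in the year before the index date, which may predate a hospital diagnosis.

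**Conclusion.** The mismatch of sources is certain on the text. As written, the rules put some patients in both groups, leave them without a start date, and let hospital-only prior CVD through to be counted as incident if it is later recorded. This is a contradiction between stated rules rather than detail left to a fuller document.

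The consequence for the estimates is uncertain in size and direction, because the article gives no HES-only share of SMI or CVD. On the assumptions shown, the RR of 1.30 over 3.2 years lies at about 1.25 to 1.30 under moderate leakage. It is 1.23 or 1.48 when every missed case is re-coded, depending on the balance between groups. Contamination of the unexposed alone does not matter. Late entry may understate early weight change, by an amount that cannot be derived.

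This should be fixed before the cohort is extracted. The evidence does not support calling the results invalid without it.

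**What to change.** Apply the same linked sources to every rule.

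1. Index date: the earliest SMI code in GP or HES data.
2. Unexposed: no SMI code in either source up to the matched index date, with follow-up censored at any later first SMI code. Replacing the word ever also stops controls from being selected on their future. That is a separate matter from the code source, but it sits in the same sentence.
3. Prior-CVD exclusion: GP or HES data before the index date, stating that coronary heart disease includes angina and acute coronary syndrome.
4. CVD outcomes: state that the date is the earliest of GP record, HES record or ONS cause of death.

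The 2-year sensitivity analysis should then run from the revised index date, in both groups. It would also help to report how many SMI and prior-CVD cases are known from HES only, since that figure decides how much this matters.

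The cost is code-list work and wording on data already planned for linkage, for a source population already restricted to linkage-eligible patients. The net change in cohort size is unknown: HES-only SMI patients gain an index date and are added, while patients with hospital-coded prior CVD are removed.
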